### Statistical analysis

3.6

All data analysis will be carried out in accordance with the principle of intentional processing. The missing value will be substituted for the last observation carried forward method. Before the analysis, 2 similar participants with complete data will be carefully checked to ensure that the data are correct.

The data will be analyzed using a social science version 22.0 statistical software packages (SPSS 22.0, Chicago, IL). The analysis method will be selected according to the distribution characteristics of the data: the measurement data will be checked using group *t* test or non-parametric test, the count data will be tested using chi-square test or Fisher exact probability method, and the score data will be tested using non-parametric test. Compared with the baseline value, paired *t* test or non-parametric test will be used to evaluate measurement data, and non-parametric test will be utilized to test count data. All statistical tests will be bilateral tests, and a *P* value <.05 will be deemed to indicate statistical significance.

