## Introduction

1

Chronic obstructive pulmonary disease (COPD) is an illness characterized by the progressive aggravation of respiratory symptoms and airflow obstruction. Its morbidity and mortality are one of the highest in the world, causing a huge burden on society and the economy.^[1]^ According to estimates by the World Health Organization (WHO), COPD will rise to the third leading cause of death in the world by 2030^[2]^ if no control measures are applied. The global initiative for chronic obstructive pulmonary disease (GOLD) uses the ratio of forced expiratory volume in 1 second to forced vital capacity (FEV_1_/FVC) <0.70 as the diagnostic criteria for airflow obstruction. On this basis, COPD is divided into 4 phases based on the degree of FEV_1_ decline,^[3]^ the proportion of GOLD I and II stages is much higher than that of III and IV.^[4]^ In a retrospective studies, Tantucci and Modina^[5]^ found that the average decline rate of FEV_1_ in GOLD II and III phases was 47 to 79 mL/yr and 56 to 59 mL/yr, respectively, and in GOLD IV, it was lower than 35 mL/yr; Bhatt et al^[6]^ also found that FEV_1_ of COPD patients with GOLD stage I decline fastest, and then gradually slowed down. With the decline of lung function, COPD patients gradually develop to skeletal muscle dysfunction, which affects the patient's athletic ability, reduces the quality of life, and produce anxiety and depression.^[7,8]^ Studies by Burkes and Drummond^[9]^ and Lee et al^[10]^ have shown that early intervention (knowledge education, drug therapy, exercise therapy, etc) for COPD can effectively delay the disease process, improve the mental state of patients, increase exercise tolerance, and reduce social and economic burdens. Therefore, it is necessary to intervene as early as possible.

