### Design

2.1

This study is a randomized, parallel, and controlled trial designed to evaluate the effectiveness of Baduanjin exercise intervention in improving lung function, exercise capacity, and quality of life in patients with mild COPD. A total of 192 patients will be recruited in Chengdu and randomly assigned to the experimental group or the control group in a 1:1 ratio. Participants in the experimental group will receive a 24-week Baduanjin exercise training intervention at least 5 days a week and 60 minutes a day, while participants in the control group will not be given any specific exercise intervention and will be told to maintain their original lifestyle for 24 weeks. The primary and secondary outcomes will be measured at baseline and at weeks 12, 24, 36, 48, 72, and 96. The participation process of this trial is shown in Fig. 1. This agreement follows the standard agreement item: Intervention Test Recommendation (SPIRIT) guidelines,^[20]^ and meets the SPIRIT list (please see Guidelines Checklist). The study flow chart is presented in Fig. 2.

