### Sample size

2.4

This study is a randomized controlled trial. The experimental group is basic treatment (health education and Tiotropium bromide) + Baduanjin exercise training, and the control group is basic treatment + maintain the original lifestyle and control the exercise. Pulmonary function (FEV_1_%) is the main outcome index. According to previous literature.^[19]^ The mean and standard deviation of FEV_1_% of the control group was 57.09 and 22.53, while the mean and standard deviation of FEV_1_% of the experimental group was 60.24 and 20.15, set *α* = 0.05 (bilateral), *β* = 0.10. The sample size N1 = N2 = 77 cases of experimental group and control group were calculated by Power Analysis and Sample Size version 15.0.5 (PASS 15.0.5 NCSS, LLC USA). Assuming a 20% dropout rate for the study subjects, 96 samples were needed. Therefore, the lowest sample size was 192.

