### Termination and withdrawal criteria

2.9

All participants will be informed of their right to withdraw from the trial and, if so, will receive standardized treatment. The reasons for the withdrawal will be recorded in their case report file (CRF). The criteria for stopping treatment and pulling patients out of the study are:

Participants have experienced exercise-related adverse events, and the researchers believed that they are unfit to exercise;Participant has another serious illness and needs to be treated during the study;The participant has suffered a severe exacerbation;Poor compliance so that exercise time is <80% of the prescribed time;Perform other pulmonary rehabilitation exercises during the study.

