### Outcome measures

3.2

Primary outcome: The primary outcome is the change in lung function from baseline to the end of the follow-up period (all time points). Including FEV_1_, FVC, FEV_1_/predicted value.

Secondary outcomes: Including COPD assessment test (CAT), 6 minute walking test (6MWT), dyspnea score (modified British medical research council dyspnea score, mMRC), and St. George Respiratory Questionnaire (SGRQ), Self-rating Depression Scale (SDS), Self-rating Depression Scale (SAS).

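### Carrying the last value forward records every leaver as having no further FEV1 decline; this biases the comparison if dropout differs by arm and can dilute a true effect if it does not

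*Protocol article*

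**What the plan says.** The Statistical analysis section states "All data analysis will be carried out in accordance with the principle of intentional processing", evidently meaning intention to treat, and then "The missing value will be substituted for the last observation carried forward method". It names no other missing-data method.

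The primary outcome (Outcome measures) is change in lung function from baseline to the end of follow-up at every time point. Under Design, outcomes are "measured at baseline and at weeks 12, 24, 36, 48, 72, and 96". The Introduction expects the outcome to fall: for GOLD II and III, mean FEV1 decline "was 47 to 79 mL/yr and 56 to 59 mL/yr, respectively", and it reports that "FEV_1_ of COPD patients with GOLD stage I decline fastest, and then gradually slowed down". GOLD I is the stage enrolled (Eligibility criteria), but no rate is given for it.

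On missingness, Sample size has "Assuming a 20% dropout rate for the study subjects", with no breakdown by arm. Termination and withdrawal criteria lists five reasons that both stop treatment and end participation. One is "Poor compliance so that exercise time is <80% of the prescribed time"; another is an exercise-related adverse event. The remaining three (another serious illness, a severe exacerbation, other pulmonary rehabilitation exercise) can occur in either arm. The control group receives no training.

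**The concern.** The trial asks whether Baduanjin slows a decline. Carrying the last value forward gives each leaver a decline of zero from the last visit onwards. An arm that loses more patients, or loses them sooner, then looks better preserved than it is.

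The withdrawal criteria make an imbalance plausible. The control arm has no prescribed exercise time to fall short of and no trial exercise to cause an adverse event. The exercise criteria also operate mainly during the 24-week training period, so many of the affected patients would have baseline, week 12 or week 24 as their last visit, and a value could be carried for 72 weeks or more. At stake is a false positive on the primary outcome or, if dropout is equal, an understated true effect.

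**Working it through.** **Inputs from the protocol.** 96 patients per arm; 20% dropout overall; last visit at week 96; decline of 47 to 79 mL/yr (the GOLD II figure, assumed here for GOLD I). The plan's dropout step reproduces closely: 77/0.80 = 96.25, against 96 stated. One overall rate is applied, which says nothing about how leavers divide between arms.

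**Inputs assumed.** Arm-specific dropout of 30%/10%, 25%/15% and 20%/20% (each averages 20%); last visit at week 24 or 12; linear decline, equal in both arms under the null; between-patient slope SD 60 mL/yr; residual SD 100 mL per measurement.

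**Decline hidden per leaver** = rate × (96 − last week)/52.
- Last seen week 24: 47 × 72/52 = 65.1 mL; 79 × 72/52 = 109.4 mL.
- Last seen week 12: 47 × 84/52 = 75.9 mL; 79 × 84/52 = 127.6 mL.

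**False week-96 benefit with no true effect** = (Baduanjin dropout − control dropout) × hidden decline.

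| Dropout, Baduanjin / control | Last seen week 24 | Last seen week 12 |
|---|---|---|
| 30% / 10% | 13.0 to 21.9 mL | 15.2 to 25.5 mL |
| 25% / 15% | 6.5 to 10.9 mL | 7.6 to 12.8 mL |
| 20% / 20% | 0 | 0 |
| 10% / 30% | −13.0 to −21.9 mL | −15.2 to −25.5 mL |

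For scale, total decline over 96 weeks is 47 × 96/52 = 86.8 mL to 79 × 96/52 = 145.8 mL, so a true 25% slowing is worth 21.7 to 36.5 mL.

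**Type I error at week 96, last visit week 24.** The variance of change is (60 × 96/52)² + 2 × 100² = 32,272 for completers and (60 × 24/52)² + 2 × 100² = 20,767 for leavers. With dropout share d, an arm's variance is (1 − d) × 32,272 + d × 20,767 + d(1 − d) × (hidden decline)². At 63 mL/yr and 30%/10%, the hidden decline is 87.2 mL and the arm variances are about 30,418 and 31,807. The standard error is √(62,225/96) = 25.5 mL, the bias is 0.20 × 87.2 = 17.4 mL, and bias/SE = 0.685. The two-sided rejection rate is Φ(−1.96 + 0.685) + Φ(−1.96 − 0.685) = 10.5%.

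| Dropout | 47 mL/yr | 63 mL/yr | 79 mL/yr |
|---|---|---|---|
| 30% / 10% | 8.1% | 10.5% | 13.6% |
| 25% / 15% | 5.8% | 6.4% | 7.1% |
| 20% / 20% | 5.0% | 5.0% | 5.0% |

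Simulation of the same model (20,000 trials per setting) agrees to within about half a percentage point. With residual SD 150 mL, the 30%/10% row falls to 6.7%, 8.0% and 9.7%.

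**Dilution when dropout is equal.** Suppose the arms diverge linearly to a true difference D at week 96. A leaver frozen at week 24 shows D × 24/96. With 20% leaving each arm, the estimate is 0.80D + 0.20 × 0.25D = 0.85D, a 15% loss.

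**The case against.** A reader might infer that the plan's own rules make the Baduanjin arm lose more patients, so that the bias must favour it. The documents do not go that far. They give no arm-specific dropout, and three of the five criteria apply to both arms. Controls are unblinded and untrained, so they may leave or take up other rehabilitation. If controls leave more often, the sign reverses. This objection stands: the direction is conditional.

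The size is also uncertain. The decline rate belongs to GOLD II, although the Introduction says GOLD I falls fastest, so it may well not be too high. Neither SD is in the protocol. A ten-point gap in dropout leaves type I error near nominal, and the bias is smaller at visits before week 96. The dilution figure needs the arms to keep diverging after training ends at week 24; if a gain is reached by then and merely held, carrying week 24 forward dilutes nothing.

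One might also argue that single imputation by itself inflates false positives because it treats carried values as observed. In the model above, equal dropout keeps the error at 5%, so the inflation shown comes from the imbalance.

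An unseen analysis plan is no answer, because the protocol does not leave the method open; it names an unsuitable one.

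**Conclusion.** The point holds in conditional form. For a declining outcome, the stated method favours whichever arm loses more patients. If losses are equal, it is unbiased under the null but shrinks a difference that continues to widen. An imbalance towards the Baduanjin arm is plausible from two withdrawal criteria; it is not stated.

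With the borrowed GOLD II rate and last visits at week 24, a 20-point imbalance produces a false benefit more than half as large as a true 25% slowing (13.0/21.7 = 0.60) and type I error of roughly 8–14%. A 10-point imbalance gives 6–7%. These figures rest on the assumed splits, SDs, linear decline and last-visit times. The unsuitability of the method does not depend on any one of them.

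**What to change.** Replace the carried-forward sentence with a likelihood-based mixed model for repeated measures on all observed visits, with treatment, visit, treatment-by-visit and baseline-by-visit terms. The MIXED procedure in the SPSS package already named can fit it. If data are missing at random and the model is correctly specified, the bias calculated above is removed.

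Missing at random is doubtful for patients removed for non-compliance or a severe exacerbation. Add a sensitivity analysis that imputes Baduanjin leavers as declining at the control rate, with a further delta shift.

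Reconcile three sections that now pull apart: Termination and withdrawal criteria, which ends participation; Statistical analysis, which promises intention to treat; and Compliance, which promises every reasonable effort at follow-up. State that outcome data collected after treatment stops enter the analysis, since a value that is measured needs no imputation.

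The cost is revised wording and a little more analysis work. The visit schedule and sample size need not change on this account. The estimate may be less favourable and its interval wider.

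### The planned group tests neither adjust for baseline nor combine the six follow-up visits, and the within-arm paired tests at P<.05 cannot show a Baduanjin effect

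*Protocol article*

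**What the plan says.** The Design section sets the schedule: "The primary and secondary outcomes will be measured at baseline and at weeks 12, 24, 36, 48, 72, and 96". The Outcome measures section defines the primary outcome: "The primary outcome is the change in lung function from baseline to the end of the follow-up period (all time points"), for three variables: "Including FEV_1_, FVC, FEV_1_/predicted value".

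The Statistical analysis section then names the tests. Between groups, "the measurement data will be checked using group *t* test or non-parametric test", and scores are compared by rank methods only. Within groups, "Compared with the baseline value, paired *t* test or non-parametric test will be used to evaluate measurement data". Missing data are handled as follows: "The missing value will be substituted for the last observation carried forward method". One threshold covers everything: "All statistical tests will be bilateral tests, and a *P* value <.05 will be deemed to indicate statistical significance".

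The section names no baseline covariate and no model for the repeated visits. It does not say whether the group test uses change or the follow-up value, nor in so many words that it is repeated at each visit. It does not mark the paired tests as descriptive.

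**The concern.** This is a stated method, not a detail left to a longer document. The article's hypothesis is that Baduanjin delays the decline of lung function, which is a between-group question about a course over time. The data for a baseline-adjusted longitudinal comparison will be collected, but none of the named tests is one.

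Two things are at stake:

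- **Precision.** An unadjusted two-sample test may discard information that costs nothing to use. Carrying the last observation forward also fills visits that a likelihood-based repeated-measures model would not need filled.
- **Interpretation.** Tests of each arm against its own baseline, judged at the same .05 level, make it easy to conclude that one arm declined and the other did not. Both arms receive tiotropium and health education. All patients enter above an FEV1 threshold of 80% predicted, so regression to the mean can occur in both arms. A before-after change in one arm therefore mixes several causes.

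**Working it through.** **Inputs.** From the Sample size section: control mean 57.09, SD 22.53; experimental mean 60.24, SD 20.15; 77 per arm before dropout; two-sided alpha 0.05; beta 0.10. Hence the difference is 60.24 − 57.09 = 3.15, the pooled SD is √[(22.53² + 20.15²)/2] = 21.37, and the midpoint of the means is 58.67. From Eligibility criteria: FEV1 at least 80% predicted. The correlation r is not given, so a range is assumed.

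**Step 1: the plan's own figure.** n per arm = 2(1.960 + 1.282)²(21.37/3.15)² ≈ 968, not 77. With 77 per arm, the power of a t test on follow-up values is about 15%. Baseline adjustment raises this to 18%, 25%, 33% or 56% at r = 0.5, 0.7, 0.8 or 0.9. Only r of about 0.96 would make 77 enough. The sample size is a separate fault, and adjustment should not be presented as its cure.

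**Step 2: precision with equal variances at baseline and follow-up.** Relative to a follow-up value, the outcome variance is 1 for an unadjusted test, 2(1 − r) for a change score and 1 − r² after baseline adjustment.

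| r (assumed) | adjusted / follow-up value: 1 − r² | adjusted / change: (1 + r)/2 |
|---|---|---|
| 0.5 | 0.75 | 0.75 |
| 0.7 | 0.51 | 0.85 |
| 0.9 | 0.19 | 0.95 |

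**Step 3: precision if entry truncates the planning distribution.** Take a normal source with mean 58.67 and SD 21.37, cut at 80. The standardized cut is (80 − 58.67)/21.37 = 0.998, so the upper 15.9% enter, with mean baseline 91.2 and baseline SD 9.54 (variance 91.0). The regression slope stays at r, and the residual variance is 21.37²(1 − r²).

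- r = 0.90: residual 86.8. Change-score variance 0.10² × 91.0 + 86.8 = 87.7, ratio 0.99. Follow-up variance 0.90² × 91.0 + 86.8 = 160.5, ratio 0.54.
- r = 0.95: residual 44.5. Change-score variance 0.05² × 91.0 + 44.5 = 44.8, ratio 0.995. Follow-up variance 0.95² × 91.0 + 44.5 = 126.7, ratio 0.35.

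Against a change score the saving is therefore about 1% or less. Against follow-up values it remains large.

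**Step 4: regression to the mean.** The expected within-arm fall with no true change is (1 − r) × (mean baseline of entrants − source mean). For the truncated planning distribution this is 0.10 × 32.6 = 3.3 points at r = 0.90 and 0.05 × 32.6 = 1.6 points at r = 0.95. Other assumed sources give less:

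| Assumed source (mean, SD) | fall at r = 0.90 | fall at r = 0.95 |
|---|---|---|
| 58.67, 21.37 | 3.3 | 1.6 |
| 80, 12 | 0.96 | 0.48 |
| 90, 10 | 0.29 | 0.14 |

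**Step 5: paired tests with no treatment effect.** Let both arms (77 each) have the same true change, in SDs of change, and let p be the chance that one paired test is significant. The chance that only the experimental arm is significant is p(1 − p).

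| Common change (SD) | p | experimental arm only |
|---|---|---|
| 0 | 0.050 | 4.8% |
| 0.1 | 0.139 | 12% |
| 0.2 | 0.410 | 24% |
| 0.3 | 0.739 | 19% |

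The chance that the arms disagree in either direction is twice this, up to about 48% at 0.2 SD.

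**The case against.** The case for leaving the plan alone has several parts:

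- **Validity.** An unadjusted two-sample test is valid under randomization, and regression to the mean acts equally on both arms, so it does not bias the group comparison. This stands. The precision issue is one of efficiency.
- **Baseline is used.** A reader might infer that the plan ignores the baseline values. It does not: the primary outcome is defined as change, and the natural reading is a group test on change. Baseline is then used, though not as a covariate, and the loss can be small.
- **The size of the gain.** A reader might put the correlation among entrants (0.68 when the source r is 0.90) into (1 + r)/2 and claim a saving of about 16% of the variance. That formula needs equal variances at baseline and follow-up, and truncation on baseline breaks this. The correct saving in that setting is about 1%.
- **Regression to the mean.** A reader might infer a fall as large as the planned 3.15 points. That holds only if the patients screened resemble the planning population. The article does not describe the screening distribution, and other assumed sources give falls well below 1 point.
- **Role of the paired tests.** They accompany the group test and do not replace it, and the article never says that a treatment effect will be inferred from them. This is fair. The fault is that they carry the same significance rule with no stated limit on their use.
- **Visit by visit.** Repeating the group test at each visit is a reasonable inference from the outcome definition, but it is not written.

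**Conclusion.** The concern holds in limited form. The article fixes unadjusted group tests and within-arm paired tests at P<.05 although a baseline and six follow-ups are available.

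The precision lost runs from about 1% of variance (change scores, truncated planning distribution, r = 0.90) to 81% (follow-up values, equal variances, r = 0.9). Where the trial falls depends on r and on which quantity is tested, and the article states neither. The further gain from modelling the visits jointly cannot be computed without the between-visit correlations.

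The firmer part is the paired tests. They do not compare the randomized groups, and significance in one arm only is not evidence of a Baduanjin effect, whatever the amount of regression to the mean. The documents do not support a claim that the group test is biased or that the sponsor intends to infer benefit from the paired tests.

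**What to change.** - Make the primary between-group analysis a repeated-measures model with treatment, visit, treatment-by-visit, baseline and baseline-by-visit. With baseline in the model, the choice between change and follow-up value no longer alters the treatment estimate.
- Fit it to the observed data. Drop the last-observation-carried-forward filling for this analysis, since running the model on filled values would undercut it.
- Report the adjusted difference with a 95% confidence interval at one time point that the sponsor prespecifies. The documents do not settle which: training ends at week 24, follow-up ends at week 96, and the outcome refers to all time points.
- Use the same model for the secondary outcomes, with an ordinal model for mMRC, and keep the rank tests as sensitivity analyses.
- State that the within-arm paired tests are descriptive and will not support a claim of effect.

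The cost is wording in the analysis section. No new visits, measurements or patients are needed.

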## Discussion

4

COPD is a major public health problem that seriously affects the quality of life of patients, even life-threatening. The sign of COPD progression is decreased lung function, and pulmonary rehabilitation has been proven to be the most effective treatment strategy for improving shortness of breath, health status, and quality of life.^[13]^ However, traditional pulmonary rehabilitation requires a series of professional evaluations to develop a perfect and personalized plan,^[22]^ so the overall effect is not satisfactory, and it is urgent to develop family-based pulmonary rehabilitation methods.^[23]^ Baduanjin is the representative of the traditional Chinese medicine guidance method, covering endurance training, breathing muscle training, stretching training, and psychological adjustment required for pulmonary rehabilitation. The whole set of movements is easy to learn, moderate intensity, and significant efficacy, which applicability and cost are much better than traditional pulmonary rehabilitation. However, previous studies have mostly focused on the efficacy of Baduanjin in the middle and late stages of COPD, and there is no unified understanding of its intervention effect in mild COPD pulmonary function decline. Therefore, this study focuses on the effect of Baduanjin on lung function in the early stage of COPD.

As far as we know, this is the first clinical study on the treatment of mild COPD with Baduanjin exercise training. In our research, we will use validated objective tools such as lung function test, COPD assessment test, 6-minute walk test, etc. These measurements improve the reliability and versatility of the results. This study has limitations. It is difficult to monitor physical activities outside the interventions of the experimental group and the control group. Although all participants are required to maintain the original lifestyle and exercise volume, this is not enough to limit activities that may affect the experimental results. Baduanjin belongs to traditional Chinese guiding Qigong, and it is unclear whether its exercise mode and intensity are suitable for people in other regions. The condition of mild COPD is related to many factors, and the influence of education management and conventional drug treatment on the efficacy of Baduanjin cannot be excluded. Despite the limitations, we believe that this study will help discover the benefits of Baduanjin in preventing lung function decline, improving exercise performance, and improving quality of life in patients with mild COPD. In the future, multicenter randomized controlled trial (RCT) and multi-dimensional comprehensive comparison should be performed.
